### Outcomes

2.5.

Professional assessors will observe primary and secondary outcomes in participants at four time points: baseline (T1), after 4 weeks of treatment (T2), after 8 weeks of treatment (T3), and 4 weeks after the end of treatment (T4) (Table 1). To ensure the quality of scale assessments and minimize inter-rater variability, assessors will undergo unified standardized training based on a pre-established operation manual before the study begins. Only after passing the training will, they be allowed to perform assessments. Each scale assessor will be responsible for only part of the assessment tasks and will be unaware of the participants’ group assignments. They will also not be involved in the intervention process or the final data statistical analysis.

**Table 1. t0001:** Trial implementation schedule.

	Study period					
	Enrollment	Allocation	Treatment phase			Follow-up
Timepoint	−1 week		0 day	4 week	8 week	12 week
**Enrollment**						
Eligibility screen	X					
Informed consent	X					
Allocation		X				
**Interventions**						
Active infrared moxibustion			X	X	X	
Sham infrared moxibustion			X	X	X	
**Assessments**						
Blood lipids		X		X	X	X
MoCA		X		X	X	X
HAMD		X		X	X	X
HAMA		X		X	X	X
PSQI		X		X	X	X
Adverse events			X	X	X	
Gut Microbiota		X			X	
Plasma TMAO		X			X	
MRI Acquisition		X			X	

MoCA: Montreal Cognitive Assessment; HAMD: Hamilton Depression Rating Scale; HAMA: Hamilton Anxiety Scale; PSQI: Pittsburgh Sleep Quality Index; TMAO: trimethylamine-N-oxide; MRI: Magnetic resonance imaging.

#### Primary outcomes

2.5.1.

The change in LDL-C from baseline to 8 weeks after intervention.

#### Secondary outcomes

2.5.2.

Other lipid profile indicators: Triglycerides, total cholesterol, and high-density lipoprotein cholesterol.Montreal Cognitive Assessment (MoCA): Suitable for rapid screening of mild cognitive impairment and other cognitive declines, with higher scores indicating better cognitive function.Hamilton Depression Rating Scale (HAMD): Commonly used to assess clinical depressive symptoms. The scale consists of 17 items with a total score of 54. Scores of 7–17 indicate mild depression, 18–24 indicate moderate depression, and >25 indicate severe depression. Higher scores indicate more severe depression.Hamilton Anxiety Scale (HAMA): Commonly used to assess clinical anxiety symptoms. The scale consists of 14 items with a total score of 70. Higher scores indicate more severe anxiety.Pittsburgh Sleep Quality Index (PSQI): Used to assess sleep quality. The scale consists of 24 items, with higher scores indicating poorer sleep quality.Safety: All adverse events occurring during the research process will be recorded by experienced acupuncturists, including their occurrence time, severity, and the measures taken for management. Potential study-related adverse events mainly encompass skin scalds and discomforts that may arise after moxibustion, such as palpitations, dizziness, etc. Researchers, in collaboration with acupuncturists, will analyze whether the occurrence of adverse events is related to the study intervention.

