#### IM group

2.4.1.

Participants in the observation group will receive infrared moxibustion intervention using an infrared moxibustion chamber (Model CH-6, Hunan Cihui Medical Technology Co., Ltd., Changsha, Hunan). Participants will lie supine with their entire body below the head and neck placed inside the infrared chamber. Infrared moxibustion will be initiated with a single button press. The temperature inside the chamber will be set to 50 °C, with a treatment duration of 40 min, once per day, twice per week, for a total of 8 weeks.

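### Table 1 schedules adverse event recording only to week 8, while sections 2.5 and 2.5.2 read together carry the safety outcome to the week-12 visit; the two should be reconciled

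*Protocol article*

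**What the plan says.** Three places in the protocol article bear on the safety window.

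- Section 2.5 (Outcomes) gives a general rule: "Professional assessors will observe primary and secondary outcomes in participants at four time points". The last two of these are "after 8 weeks of treatment (T3), and 4 weeks after the end of treatment (T4) (Table 1", and the sentence points to Table 1 for the schedule.
- Section 2.5.2 (Secondary outcomes) includes Safety in its list and states: "All adverse events occurring during the research process will be recorded by experienced acupuncturists". Onset time, severity and the measures taken are to be noted. Nothing limits this to the treatment phase, and no week or visit is named.
- Table 1 has an adverse event row with three marks, under day 0, week 4 and week 8. Its week-12 cell is empty. The rows for blood lipids, MoCA, HAMD, HAMA and PSQI are all marked at week 12.

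On treatment duration, section 2.4.1 specifies sessions "once per day, twice per week, for a total of 8 weeks", so the last session falls at about week 8.

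**The concern.** Section 2.5 refers to Table 1, yet for one of the secondary outcomes the table does not follow the rule in that section. A site reading the text would ask about adverse events up to the last visit. A site reading the table would stop at week 8. With three centres, both readings could be used in the same trial.

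What is at stake is how complete and uniform the safety record is after the last session. An event that starts in weeks 8 to 12, or one open at week 8 whose outcome is not yet known, has no planned occasion on which it would be asked about. Section 2.5.2 assigns the recording to acupuncturists, and treatment has ended by then. The only activities that Table 1 schedules at week 12 are the lipid sample and the four scales. Recording in that interval would rest largely on what participants volunteer. The lipid, cognitive, mood and sleep outcomes would be followed to week 12 and scheduled safety recording only to week 8, with no reason given for the difference.

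**Working it through.** **Inputs**

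- Treatment duration: 8 weeks (section 2.4.1).
- Last assessment, T4: 4 weeks after the end of treatment (section 2.5).
- Table 1 time columns from the start of treatment: day 0, week 4, week 8, week 12.
- Adverse event row of Table 1: marks at day 0, week 4 and week 8.
- Session frequency: twice per week (section 2.4.1).

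**Step 1: reproduce the timing of the last visit.** 8 + 4 = 12 weeks. This agrees with the last column of Table 1, so text and table mean the same T4 visit.

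**Step 2: check that the empty cell is real.** Lining the rows up with the header gives:

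| Row | Allocation | Day 0 | Week 4 | Week 8 | Week 12 |
|---|---|---|---|---|---|
| Active and sham intervention | | X | X | X | |
| Blood lipids | | | | | |
| – marks | X | | X | X | X |
| Adverse events | | X | X | X | |

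The blood lipid row has its four marks where section 2.5 leads one to expect them, including week 12. The alignment is therefore sound, and the blank in the adverse event row is not an artefact of reading the table from PDF.

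**Step 3: size of the gap.** Last scheduled adverse event mark: week 8. Last visit: week 12. Gap = 12 − 8 = 4 weeks. As a share of the time from day 0, 4/12 = 33.3%. If the screening week is counted, 4/13 = 30.8%.

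**Step 4: what the marks can mean.** Twice per week for 8 weeks is 2 × 8 = 16 sessions, against three adverse event marks. The marks can hardly be the only occasions on which an event is written down. They are better read as scheduled points, with event-driven recording around them. On that reading, a week-4 or week-8 mark can look back over the preceding interval, while no mark looks back over weeks 8 to 12.

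**The case against.** The strongest counter-argument is that Table 1 may intend collection during treatment only. The adverse event marks coincide exactly with the two intervention rows. The events anticipated in section 2.5.2 (skin scalds, palpitations, dizziness) are tied to sessions, and there are no sessions after week 8. The rule in section 2.5 also fits safety poorly: it concerns professional assessors and starts at a pre-treatment baseline, whereas adverse events are recorded by acupuncturists and the row begins at day 0. The rule may have been written with the lipid and scale measures in mind. All of this stands as a plausible account of intent. But the text nowhere states a treatment-phase limit, and its wording is broader than one, so text and table need reconciling whichever was meant.

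Three stronger readings are tempting, and the document does not support them.

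- A reader might infer that section 2.5.2 itself demands collection at week 12. It names no week. The week-12 requirement comes only from joining section 2.5 to the listing of Safety as a secondary outcome, helped by the open wording of 2.5.2.
- A reader might infer that events after week 8 will be lost because the schedule determines the visit forms. The article says nothing on how the forms are built. Section 2.6 covers only their completion, review and double entry, and the sentence in 2.5.2 still permits later events to be recorded.
- A reader might take 33% as the proportion of safety information missing. Those weeks contain no device exposure, and the document gives no basis for any number or share of missed events.

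**Conclusion.** The inconsistency holds. Section 2.5.2, read with section 2.5, carries the safety outcome to T4, and Table 1 schedules its recording only to week 8. The size is 4 of 12 calendar weeks without a scheduled recording point. It applies by design to all 158 planned participants, though fewer may reach week 12, since section 2.7 allows for 20% dropout.

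The conclusion rests on two assumptions: that Safety falls under the general rule in 2.5 because it is listed as a secondary outcome, and that the research process includes the follow-up period. Both are natural readings, but neither is spelled out. The primary outcome, LDL-C change to week 8, and its analysis are untouched. This is a modest point, worth acting on because it changes what is collected and is cheap to put right before follow-up is complete.

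**What to change.** Add an adverse event mark in the week-12 column of Table 1, and ask the same standard adverse event question, in the same words, in both arms at the T4 visit. The question should cover events that began after week 8 and the outcome of events still open at week 8. State who asks it, because section 2.5.2 names the acupuncturists and their sessions have ended by then.

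The cost is one mark in the table and a short piece of extra recording at a visit already scheduled for lipids and scales. No further visit is needed, and neither the sample size nor the primary analysis changes.

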#### Exploratory secondary endpoints

2.5.3.

##### Gut microbiota

2.5.3.1.

Fecal samples will be collected from participants at baseline and after 8 weeks of treatment and stored in a −80 °C freezer. Total genomic DNA of the fecal microbiota will be extracted according to the QIAamp Fast DNA Stool Mini Kit operation manual. DNA concentration and purity will be assessed using a microplate reader, and DNA integrity will be detected by gel electrophoresis. The 16S V3-V4 region will be amplified using 341 F and 806 R primers, and 16S library construction will be performed according to the Illumina library construction strategy. Preliminary quantification will be performed using Qubit 3.0, library insert size will be detected using Agilent 2100, and accurate quantification will be performed using Q-PCR. After the library passes quality control, MiniSeq high-throughput sequencing will be performed. Alpha diversity will be assessed using the Observed species, Chao1, Shannon, and Simpson indices. Beta diversity will be compared using weighted and unweighted UniFrac distances, and differences in microbiota structure within and between groups will be evaluated using principal coordinate analysis (PCoA) in R software (version 3.5.3).

##### Plasma TMAO

2.5.3.2.

Participants will fast starting at 8 PM the night before blood collection. At 8 AM the next morning, a 6 mL fasting venous blood sample will be drawn from the elbow vein after 12 h of fasting. Of this, 3 mL will be centrifuged to obtain serum for lipid measurement; the other 3 mL will be anticoagulated and centrifuged to obtain plasma samples, which will be immediately placed in a −80 °C freezer for TMAO detection. Changes in TMAO levels in participants will be detected at baseline and after 8 weeks of treatment. Plasma TMAO content will be detected using liquid chromatography-mass spectrometry, with TMAO content quantified by peak area. Larger peak areas indicate higher TMAO content.

##### MRI acquisition and analysis

2.5.3.3.

MRI scans were performed at baseline and 8 weeks after the intervention. Magnetic resonance imaging data will be acquired using a Siemens Verio 3.0 T MR scanner (Siemens, Germany). During scanning, participants will lie supine on the examination table with their head fixed and use specialized sponge ball earplugs to reduce noise. They will be instructed to breathe calmly, relax both physically and mentally, place their hands by their sides, and naturally separate their legs. They should maintain a fixed body position and avoid movement throughout the scanning process. Scanning parameters include: TR = 2530 ms, TE = 2.01 ms, flip angle (FA) = 7°, field of view (FOV) = 256 mm × 256 mm, matrix = 256 × 256, slice thickness = 1 mm.

Further processing of the T1 structural image data was performed using SPM12 software (Statistical Parametric Mapping, Wellcome Trust Centre for Neuroimaging, London, UK) and its CAT12 toolbox (Computational Anatomy Toolbox) on the MATLAB platform (The MathWorks Inc., Natick, MA, USA). The main steps included: (1) Data format conversion and preparation; (2) Segmentation of the images into gray matter, white matter, and cerebrospinal fluid; (3) Spatial registration and normalization to the Montreal Neurological Institute standard space using the DARTEL algorithm; (4) Image quality inspection; (5) Spatial smoothing with an 8 mm full-width at half-maximum Gaussian kernel.

### Data collection and management

2.6.

After full communication, participants will sign informed consent forms. Case report forms must be promptly completed and signed by assessors and corresponding researchers. After the project manager reviews the completed case report forms, data entry will be performed by two data entry clerks to reduce bias caused by data entry errors. The original case report forms will then be uniformly managed by the project manager.

### Sample calculation

2.7.

The sample size for this study was calculated using G*Power 3.1.9.7 software based on existing research on moxibustion for treating hyperlipidemia. According to previous trial results [37], the LDL-C levels after intervention in the moxibustion group and the control group were 4.41 ± 0.52 mmol/L and 3.72 ± 0.43 mmol/L, respectively. With a two-tailed test value of α = 0.05 and a power of 0.95, the sample size per group was calculated to be *n* = 66. Considering a 20% dropout rate, the required sample size per group is 79, resulting in a total required sample size of 158 for this study.

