Based on existing preclinical and clinical evidence, we propose the following anticipated results. First, regarding the primary outcome, we anticipate that an 8-week IM intervention will significantly reduce LDL-C levels in patients with mild HLP compared to the sham control group. This expectation is similar with previous clinical studies. Second, concerning secondary outcomes, we expect that IM will simultaneously improve cognition, emotional state, and sleep quality in participants, consistent with previous research findings [61–63]. Patients with hyperlipidemia often suffer from impaired vascular endothelial function and increased blood viscosity, leading to cerebral microcirculatory disturbances. Previous studies have demonstrated that infrared moxibustion can promote blood circulation and reduce blood viscosity [64], which may, to a certain extent, enhance cognitive function, alleviate anxiety and depression, and improve sleep quality in patients. Finally, regarding exploratory mechanistic outcomes, we anticipate that the mechanisms underlying the efficacy of infrared moxibustion may involve the regulation of gut microbiota structure, reduction of the gut microbiota metabolite TMAO levels, and improvement in brain volume.

The findings of this study hold significant clinical translational value and public health implications. On the one hand, IM is expected to serve as a complementary therapy for clinical intervention in mild hyperlipidemia, effectively delaying the progression of dyslipidemia, reducing the long-term risk of cardiovascular and cerebrovascular diseases as well as cognitive impairment, and alleviating the public health and medical burden. On the other hand, IM devices are cost-effective and easy to operate. following standardized training, they can be widely adopted in community health centers and even for home use. This is particularly applicable in regions with uneven distribution of medical resources, demonstrating strong grassroots applicability and public health value.

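### Section 2.7 does not reproduce its own sample size: the printed inputs give 14 per group, not 66, and the printed arm order contradicts the hypothesis

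*Protocol article*

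**What the plan says.** Section 2.7 (Sample calculation) bases the sample size on one earlier moxibustion trial, in which "the LDL-C levels after intervention in the moxibustion group and the control group were 4.41" and 3.72; the figures in full are "4.41 ± 0.52 mmol/L and 3.72 ± 0.43 mmol/L, respectively". It continues "With a two-tailed test value of α = 0.05 and a power of 0.95", and reports that "the sample size per group was calculated to be" 66. An allowance of 20% for dropout brings this to 79 per group and 158 in total. The software named is G*Power. Section 2.2 gives 1:1 allocation. No other effect size, SD or assumption about change scores appears in the article.

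The primary outcome in section 2.5.1 is "The change in LDL-C from baseline to 8 weeks after intervention". The introduction hypothesises that infrared moxibustion lowers blood lipids, and the Discussion (section 3) says "we anticipate that an 8-week IM intervention will significantly reduce LDL-C levels" relative to sham. The limitations paragraph of the Discussion confirms that the sample size rests on LDL-C.

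**The concern.** Section 2.7 prints everything a two-group comparison of means needs, so its result should follow from its inputs. A difference of 0.69 mmol/L against SDs of about 0.5 is a very large standardised effect and should need far fewer than 66 per group. Either the printed means and SDs were not what was entered in the software, or the printed result belongs to another calculation.

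The word linking the two means to the two arms also gives moxibustion the higher post-treatment LDL-C, the reverse of what the trial expects.

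What is at stake is the justification of the sample size. A reader, funder or ethics committee cannot tell which LDL-C difference the trial was planned to detect, and cannot verify the 95% power.

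**Working it through.** **Inputs** (section 2.7 unless noted): means 4.41 and 3.72 mmol/L; SDs 0.52 and 0.43; two-sided alpha 0.05; power 0.95; 1:1 allocation (section 2.2); stated result 66 per group.

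**Step 1. Standardised difference.**
- Difference = 4.41 − 3.72 = 0.69 mmol/L.
- Pooled SD = √((0.52² + 0.43²)/2) = √((0.2704 + 0.1849)/2) = 0.477.
- d = 0.69/0.477 = 1.446.

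**Step 2. Attempt to reproduce 66.**
- Normal approximation: n = 2 × ((1.960 + 1.645)/1.446)² = 12.4, so 13 per group.
- Noncentral t (the two-group t-test in G*Power): 13 per group gives 94.2% power and 14 gives 95.7%, so n = 14.
- The stated 66 is 66/14 = 4.7 times this.

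**Step 3. Other readings, at two-sided 0.05 and 95% power (noncentral t).**

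| SD used | n per group |
|---|---|
| 0.43 (one arm only) | 12 |
| 0.477 (pooled) | 14 |
| 0.52 (one arm only) | 16 |
| 0.675 = √(0.52² + 0.43²), not halved | 26 |
| 0.95 = 0.52 + 0.43 | 51 |

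Allowing for a rank test (efficiency 0.955 or 0.864) raises 14 only to about 15 to 17. If 66 is read as a total, 33 per group would need d of about 0.90, which is not stated either. No variant tried at the stated alpha and power gives 66.

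**Step 4. The effect to which 66 corresponds.** Solving the noncentral-t power for n = 66 at 95% gives d = 0.632. At the pooled SD this is 0.632 × 0.477 = 0.30 mmol/L. If the difference were 0.69, the SD would have to be 0.69/0.632 = 1.09. None of these values is in the article.

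**Step 5. Power of 66 at the printed effect.** With d = 1.446 and 66 per group, power exceeds 99.99%.

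**Step 6. Dropout.** 66 × 1.2 = 79.2, printed as 79. Dividing instead, 66/0.8 = 82.5, so 83. With 20% loss, 79 × 0.8 = 63.2, so about 63 evaluable per arm. At the implied d of 0.632 their power is about 94%.

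**Step 7. What 158 delivers with 63 evaluable per arm.** The detectable d is 0.647 at 95% power and 0.503 at 80%. If the SD is 0.48, that is 0.647 × 0.48 = 0.31 and 0.503 × 0.48 = 0.24 mmol/L. The 0.48 is an assumption: it is the pooled post-treatment SD, and it equals the SD of change only if the baseline-to-week-8 correlation is 0.5, since SD of change = SD × √(2(1 − r)).

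**Step 8. Direction.** As printed, moxibustion minus control is +0.69 mmol/L, whereas the introduction and the Discussion expect a negative difference. Exchanging the labels leaves |d| at 1.446, so a two-sided n stays at 14.

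**The case against.** The strongest reply is that nothing goes wrong for the trial. If 0.69 mmol/L is the real target, 158 is more than ample, and the fix changes no patient number. That stands. A reader might infer that the trial is underpowered, and the documents do not support this. What remains is that the power claim does not follow from the effect given for it.

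A second reply is that a journal article condenses the full protocol. That would excuse a missing detail, but here both the inputs and the result are printed and they disagree.

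Four stronger readings are tempting and should not be drawn:
- **The planning effect shows harm.** The cited trial is not at hand, a transposition of the arms is quite possible, and the calculation is two-sided. The text supports a request to check the labels and no more.
- **The source population differs because 4.41 lies above the 4.1 limit for mild LDL-C elevation.** Section 2.3.1 lets a patient qualify on triglycerides or total cholesterol alone, so LDL-C outside 3.4 to 4.1 is possible in this trial too. For the same reason, 0.69 cannot be expressed as a percentage fall from that band.
- **Using post-treatment levels rather than change explains the error.** It does not. Under randomisation the expected difference between groups is the same for both, and at a correlation of 0.5 the SDs coincide. Stating the SD of change is good practice but closes none of the gap between 14 and 66.
- **A null result could not be interpreted.** It could, from its confidence interval.

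**Conclusion.** The point holds as an error in the stated sample-size calculation. The inputs printed in section 2.7 give 14 per group (13 by normal approximation), not 66. The effect that 66 implies at 95% power, d of about 0.63, is disclosed nowhere. The stated 95% power therefore cannot be verified from the article. Separately, the printed arm means contradict the expected direction of effect; this is an internal contradiction, possibly a simple transposition, and it does not account for the 66.

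The re-derivation uses only printed figures and the standard two-sample t-test. The detectable differences in mmol/L rest in addition on an assumed SD of 0.48 and on the protocol's own 20% loss. The defect must be corrected because this paragraph is the only justification for the sample size, but it gives no reason to change the number enrolled.

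**What to change.** Keep 158 and rewrite section 2.7:

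1. Check the cited trial and correct the arm labels if they are transposed.
2. State the difference and the SD actually entered in G*Power, preferably for the primary endpoint (change in LDL-C from baseline to week 8), and confirm that they return the stated number.
3. Remove 4.41 versus 3.72 as the basis unless it reproduces that number.
4. Restate what 158 delivers. With 20% loss, about 63 per arm give 95% power for d of about 0.65 and 80% power for d of about 0.50. In mmol/L this is about 0.31 and 0.24 if the SD is 0.48. That SD is only a placeholder built from the cited trial, and the authors should replace it with their own SD of change.

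The cost is one recalculation and a revised paragraph. No patients are added and the design does not change.

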**Patient and methods:**

This study will recruit 158 patients with mild hyperlipidemia and randomly assign them to either a genuine infrared moxibustion group or a sham infrared moxibustion group. The intervention will be administered twice weekly for a total of 8 weeks. Blood lipid levels, Montreal Cognitive Assessment scores, Hamilton Depression Rating Scale scores, Hamilton Anxiety Scale scores, and Pittsburgh Sleep Quality Index scores will be compared between the two groups before treatment, and at 4, 8, and 12 weeks post-treatment. Additionally, changes in gut microbiota, the gut microbiota metabolite trimethylamine N-oxide (TMAO), and brain gray matter volume will be detected and compared between the two groups before treatment and at 8 weeks post-treatment (See Graphic Abstract).

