### Randomization, allocation concealment, and blinding

2.2.

Central stratified randomization will be employed using SAS 9.3 (SAS Institute Inc., Cary, NC, USA) statistical software to generate random numbers. Eligible participants will be randomly assigned to the IM group and the sham IM group in a 1:1 ratio through a central randomization system. The central randomization system will be managed by independent personnel who will not be involved in participant recruitment, intervention delivery, outcome assessment, or statistical analysis to prevent selection bias. Both participants and the treating physicians will be blinded to the treatment allocation between active infrared moxibustion and sham infrared moxibustion. Throughout the data collection and analysis process, assessors and statisticians will also be blinded to the treatment allocation.

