### Statistics

2.8.

All data obtained in this study will be analyzed using SPSS 25.0 (SPSS Inc., Chicago, IL, USA). The analysis will be conducted using the Intention-to-Treat (ITT) analysis approach. Continuous data that conform to a normal distribution will be described using the mean ± standard deviation; otherwise, the median (interquartile range) [Median (Inter Quartile Range), M(IQR)] will be used. Categorical data will be analyzed and described using frequencies. The specific analysis is as follows.

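### The 20% dropout allowance does not preserve the stated 66 per group: 79 per group leaves about 63 and covers a loss of only 16.5%

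*Protocol article*

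**What the plan says.** Section 2.7 (Sample calculation) of the protocol article proceeds in three steps.

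- It takes post-intervention LDL-C from an earlier trial, in which the values for "the moxibustion group and the control group were 4.41 ± 0.52 mmol/L and 3.72 ± 0.43 mmol/L, respectively".
- For a two-sided 5% significance level and 95% power, it reports that "the sample size per group was calculated to be *n* = 66".
- It then allows for loss: "Considering a 20% dropout rate, the required sample size per group is 79", which doubles to 158.

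No formula is given for the allowance. Allocation is 1:1 (section 2.2). The total reappears as the recruitment target in the Abstract ("This study will recruit 158 patients with mild hyperlipidemia") and in section 2.1. For the analysis, section 2.8 says: "The analysis will be conducted using the Intention-to-Treat (ITT) analysis approach". Section 2.8.2 adds multiple imputation and a linear mixed model over the four time points.

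**The concern.** A dropout rate is a proportion of those enrolled. If a calculation requires m participants with outcome data and expects a fraction q to be lost, it must enrol m/(1 − q). Multiplying by (1 + q) takes the fraction from the wrong base and always gives too few. The stated 79 looks like the second calculation.

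The article prints both the starting number and the dropout rate, so this is a result that does not follow from its own inputs. It does not depend on detail left to a fuller protocol or to an analysis plan. At stake is whether the recruitment target does what section 2.7 says it does. The same multiplication would also carry over to any revised starting number.

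**Working it through.** **Inputs, all from section 2.7:** 66 per group before loss; 20% dropout; 79 per group and 158 in total after the allowance; two-sided α = 0.05; power 0.95; means 4.41 and 3.72 mmol/L; SDs 0.52 and 0.43.

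**1. Reproducing the stated 79**
- 66 × (1 + 0.20) = 79.2, which rounds to 79, and 2 × 79 = 158. This matches.
- 66 / (1 − 0.20) = 82.5, which rounds up to 83, and 2 × 83 = 166. This does not match.

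The printed number is therefore consistent with multiplication by 1.2. That is an inference, since no formula is stated.

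**2. What 79 per group delivers**
- Remaining after 20% loss: 79 × 0.80 = 63.2, about 63, which is 3 below 66.
- Rounding does not explain the gap: 80 × 0.80 = 64, still below 66.
- Check on 83: 83 × 0.80 = 66.4, which keeps 66.
- Largest loss at which 79 still leaves 66: (79 − 66)/79 = 13/79 = 16.5%.
- Shortfall in enrolment: 83 − 79 = 4 per group, 8 in total.

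**3. Whether power is affected**

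This depends on what 66 represents, so the 66 was checked against its own inputs.
- Absolute difference: 4.41 − 3.72 = 0.69.
- Pooled SD: √[(0.52² + 0.43²)/2] = 0.477.
- Standardised effect: d = 0.69/0.477 = 1.446.
- Normal approximation, n = 2(1.960 + 1.645)²/1.446² = 12.4, so 13 per group. The exact two-sample t-test gives 14.
- Variants: one-sided at 95% power, 11 (normal) or 12 (t-test); two-sided at 99% power, 18 (normal).

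None of these gives 66. The power consequence therefore has two very different readings.

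| Assumed effect | Source | Needed for 95% power, per group | Power with 63 per group |
|---|---|---|---|
| d = 1.446 | printed means and SDs | 14 | above 99.9% |
| d ≈ 0.632 | back-solved by assuming that 66 is exactly the 95% requirement; not in the protocol | 66 | 94.1% |

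**The case against.** Three objections deserve an answer.

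**The analysis is intention-to-treat with multiple imputation, so nobody is lost.** Participants do stay in the analysis set, and someone who leaves after week 4 contributes baseline and week-4 LDL-C, so the effective information may be somewhat more than 63 per group. But imputation does not restore a week-8 value that was never measured, and the protocol claims no such gain. By adding a dropout allowance at all, section 2.7 treats loss as costing information, and the allowance must then be computed correctly. What stands is a matter of wording: 63 is the expected number with week-8 LDL-C, not the size of the analysis set.

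**The 66 is itself unexplained, so a shortfall against it means little.** This largely stands as regards power. A reader might infer that the trial is underpowered, or that power drops from 95% to 94%. The documents support neither. On the printed means and SDs, 63 per group is far more than enough, and 79 could lose 65/79 = 82% and still leave 14. The 94% needs an effect that the protocol never states and that is less than half the printed one. The objection does not rescue the allowance, however: 66, 20% and 79 remain mutually inconsistent wherever the 66 came from.

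**The effect is trivial.** It is small: 3 fewer per group than stated, and at most about one percentage point of power on the back-solved effect. That supports correcting the sentence, not enlarging the trial.

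**Conclusion.** The dropout allowance in section 2.7 is wrong on its own figures. With 79 per group and 20% loss, about 63 per group remain, not 66. Preserving 66 would take 83 per group (166 in total), and 79 covers a loss of 16.5%. This rests only on the three printed numbers and on the usual meaning of a dropout rate as a proportion of those enrolled. No other part of the article corrects it.

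The effect on power is undetermined. It would be a fall from 95% to about 94% only if 66 were exactly the 95% requirement. On the printed means and SDs there is no shortfall at all. This is a minor but certain error in a figure that sets the recruitment target.

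**What to change.** Keep 158 and replace the dropout sentence in section 2.7 with, for example: *79 per group preserves 66 per group with outcome data for dropout up to 16.5% (13 of 79).*

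The 66 needs re-deriving in any case, since it does not follow from the printed inputs. When that is done:
- divide by (1 − dropout) rather than multiplying by (1 + dropout);
- if 20% dropout is still expected and 158 is kept, base the power statement on about 63 per group with week-8 LDL-C, and state the effect size and SD that it assumes;
- do not print a 94% power figure, because it would tie the trial to an unstated effect and entrench the unexplained 66.

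The immediate cost is one sentence and a slightly less favourable stated tolerance for dropout. Recruitment, conduct and analysis do not change.
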